### Interventions

2.4

All participants enrolled in this trial will be antidepressant-naïve before enrollment. In China, traditional Chinese medicine is commonly used either alone or in combination with antidepressants for the treatment of depression. Therefore, this trial will adopt a stratified design according to whether paroxetine is initiated after enrollment. Before randomization, qualified psychiatrists at each study center will determine whether paroxetine is clinically indicated, based on clinical assessment and discussion with the participant. This decision will not be influenced by subsequent allocation to MSNP or placebo. Within each stratum, participants will be randomly assigned in a 1:1 ratio to receive either MSNP granules or placebo granules. Accordingly, this design will generate four treatment conditions: MSNP alone, placebo alone, MSNP plus paroxetine, and placebo plus paroxetine.

Participants in the combination-therapy stratum will receive paroxetine for 6 weeks. The dosing regimen will be 10 mg once daily on Days 1–2, followed by 20 mg once daily from Day 3 onward, taken orally as a whole tablet after breakfast. Dose adjustment will be allowed according to clinical response and tolerability, with a maximum daily dose of 50 mg. Paroxetine tablets will be supplied by Zhejiang Huahai Pharmaceutical Co., Ltd., with the National Medical Products Administration approval number H20031106.

Participants in the intervention group will receive MSNP granules, whereas those in the control group will receive placebo granules. The placebo granules will contain 5% MSNP granule material blended with pharmacologically inert excipients to mimic the appearance, odor, taste, and texture of MSNP. Both MSNP and placebo granules will be manufactured by Sichuan Neo-Green Pharmaceutical Technology Development Co., Ltd. In accordance with Good Manufacturing Practice requirements and relevant National Medical Products Administration regulations. The two formulations will be indistinguishable in appearance, texture, odor, and taste.

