### Safety assessment

2.7

Throughout the study period, adverse events (AEs) will be monitored, documented, and managed in accordance with the International Conference on Harmonization-Good Clinical Practice (ICH-GCP) guidelines (Zemsi et al., 2024). AEs are defined as any unfavorable medical occurrence in a participant during the study, including symptoms, signs, diseases, or abnormalities in laboratory test results. Laboratory safety assessments will include routine blood tests and biochemical parameters (hepatic function, renal function, and electrolytes), conducted at baseline and at Weeks 2, 4, 6, and 10. Twelve-lead electrocardiograms will be performed at baseline, Week 4, and Week 10.

All AEs will be coded using the Medical Dictionary for Regulatory Activities (MedDRA) and graded according to the Common Terminology Criteria for Adverse Events (CTCAE), version 5.0, issued by the National Cancer Institute (Spencer et al., 2022). Events of Grade 3 or higher will be classified as serious adverse events (SAEs). All SAEs will be reported to the principal investigator and the institutional review board within 24 h of initial awareness. Appropriate medical management will be provided as required, and all AEs will be followed until resolution, stabilization, or clinical insignificance. Investigators may modify the dosage or discontinue administration of the investigational product at their discretion, based on the severity of the AE and its assessed causality.

The causal relationship between AEs and the investigational product will be assessed using the World Health Organization–Uppsala Monitoring Centre (WHO-UMC) system (Behera et al., 2018). Particular attention will be paid to known adverse reactions associated with paroxetine, such as fatigue, sweating, nausea, decreased appetite, somnolence, dizziness, insomnia, tremor, nervousness, and sexual dysfunction. For MSNP granules, gastrointestinal adverse events including nausea, diarrhea, and abdominal discomfort will be closely monitored. All AEs will be comprehensively documented, including onset time, duration, severity, management, clinical outcome, and their assessed relationship to the investigational product.

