According to this meta-analysis, in the non-paroxetine stratum, the expected total effective rates were 59.6% for MSNP alone and 37.0% for placebo alone, corresponding to a projected risk ratio of 1.61. In the paroxetine stratum, the expected total effective rates were 91.6% for MSNP plus paroxetine and 79.0% for placebo plus paroxetine, corresponding to a projected risk ratio of 1.16. Using the “Tests for Two Proportions” module in PASS version 21, with a two-sided alpha of 0.05, 80% power, equal allocation within each stratum, and an assumed dropout rate of 15%, the required sample sizes were 180 participants for the non-paroxetine stratum and 288 participants for the paroxetine stratum. Therefore, the final total sample size was set at 468 participants. In the non-paroxetine stratum, 90 participants will receive MSNP alone and 90 will receive placebo alone. In the paroxetine stratum, 144 participants will receive MSNP plus paroxetine and 144 will receive placebo plus paroxetine. Overall, 234 participants will receive MSNP-containing interventions (intervention group), and 234 participants will receive the corresponding placebo-containing control interventions (control group).

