### Statistical analysis

2.14

All efficacy analyses will be performed according to the intention-to-treat (ITT) principle in all randomized participants. Safety analyses will be conducted in all participants who initiate protocol-defined treatment. Missing outcome data will be handled using multiple imputation under the missing-at-random assumption.

The primary outcome (total effective rate) will be analyzed using a log-binomial regression model to estimate the adjusted RR and corresponding 95% confidence interval (CI) between the intervention and control groups. The model will include study center and concomitant paroxetine use as covariates. An interaction term between treatment group and paroxetine use will be included to assess the potential moderating effect of antidepressant co-administration on the intervention effect. Sensitivity analyses will include a predefined per-protocol (PP) analysis to assess the robustness of the findings. The PP population will include participants who complete the entire treatment course without major protocol violations and have available primary outcome data. Prespecified subgroup analyses will be performed according to baseline sex (male vs. female), age (≤55 vs. >55 years), depression severity (mild vs. moderate), NSCLC stage (I vs. II vs. III), and KPS score (70–80 vs. 90–100).

For other outcomes, repeated-measures continuous variables such as HAMD-17, PHQ-9, and GAD-7 scores will be analyzed using linear mixed-effects models to evaluate longitudinal changes from baseline between groups. The models will include group, time, group-by-time interaction, and baseline score as fixed effects, and participant and study center as random effects. For single-timepoint continuous variables such as inflammatory markers and neurotransmitters, between-group comparisons will be conducted using independent-samples t-tests or Mann–Whitney U tests, depending on data distribution. For time-to-event outcomes including PFS and OS, Cox proportional hazards models will be used to estimate hazard ratios and 95% CIs, adjusting for study center and paroxetine use. For categorical outcomes such as AE incidence and depression remission rate, group comparisons will be conducted using the chi-square test or Fisher’s exact test, as appropriate.

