## Discussion

3

This study is a nationwide, multicenter, randomized, double-blind, placebo-controlled clinical trial designed to systematically evaluate the efficacy, safety, and potential mechanisms of MSNP in the treatment of postoperative mild-to-moderate depression in patients with NSCLC. The trial is based on a rigorous methodological design, integrating multidimensional efficacy assessments and omics-based mechanistic analyses. It aims to address the current lack of high-quality clinical evidence for TCM interventions in depression.

Grounded in real-world clinical practice, this study adopts a design that ensures both scientific rigor and clinical applicability. First, it employs a strict randomized, double-blind, placebo-controlled design and is conducted collaboratively across nine research centers in different provinces of China, ensuring strong external validity and generalizability. Second, the study stratifies participants based on concomitant paroxetine use, with the aim of achieving two key objectives. The first is to evaluate the efficacy and safety of MSNP monotherapy as a viable alternative for patients who are unwilling or unable to tolerate antidepressants. The second is to explore the potential synergistic effects or mitigation of side effects when MSNP is combined with standard pharmacotherapy. This dual-scenario design enables a comprehensive appraisal of MSNP’s clinical value in personalized treatment strategies. In addition, the study includes multidimensional efficacy endpoints covering depression, anxiety, sleep disturbance, fear of recurrence, quality of life, and cancer survival. Multiple timepoint assessments are used to capture the psychological and physiological effects of MSNP in a comprehensive manner.

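### The stated adverse-event comparison, naturally read as pooled over the paroxetine strata, answers neither of the two stratum-specific safety aims and can dilute or mask an effect confined to one stratum

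*Protocol article*

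**What the plan says.** Section 2.4 (Interventions) explains that "this design will generate four treatment conditions: MSNP alone, placebo alone, MSNP plus paroxetine, and placebo plus paroxetine". Section 2.9 (Sample size estimation) sizes the two strata separately, at 90 versus 90 without paroxetine and 144 versus 144 with it, and then labels the combined groups: "Overall, 234 participants will receive MSNP-containing interventions (intervention group), and 234 participants will receive the corresponding placebo-containing control interventions (control group".

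The Discussion ties the stratification to two aims, each with a safety part. "The first is to evaluate the efficacy and safety of MSNP monotherapy as a viable alternative" concerns patients who do not take an antidepressant. The second is to "explore the potential synergistic effects or mitigation of side effects when MSNP is combined with standard pharmacotherapy".

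Section 2.7 (Safety assessment) lists known paroxetine reactions separately and adds: "For MSNP granules, gastrointestinal adverse events including nausea, diarrhea, and abdominal discomfort will be closely monitored".

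Section 2.14 (Statistical analysis) gives one comparative method for AEs: "For categorical outcomes such as AE incidence and depression remission rate, group comparisons will be conducted using the chi-square test", with Fisher's exact test as the alternative. No stratum, covariate or effect estimate is named there. In the same section the primary model is more structured: "An interaction term between treatment group and paroxetine use will be included". The survival models are adjusted for paroxetine use and yield hazard ratios with 95% confidence intervals.

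**The concern.** Each safety aim belongs to one stratum. Safety of MSNP alone is a contrast of MSNP alone with placebo alone. Mitigation of side effects is a contrast of MSNP plus paroxetine with placebo plus paroxetine. A test of all MSNP-containing arms against all placebo arms has a different null hypothesis: equal AE incidence in a population that is about 38% non-paroxetine (180 of 468) and 62% paroxetine (288 of 468). Neither aim asks that question.

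At stake is what the trial can say about harm. An AE excess confined to MSNP alone is averaged with a larger stratum in which many participants may have AEs anyway. A reduction confined to the paroxetine stratum is averaged with a stratum that has no paroxetine reactions to mitigate. In either case the pooled result may show little, although one of the stated questions has a clear answer in the data.

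**Working it through.** **Inputs from the protocol (section 2.9).** 90 per arm without paroxetine, 144 per arm with it, 234 per arm overall; two-sided alpha 0.05, 80% power, 15% dropout. No AE rate and no AE power is stated, so there is no AE figure to reproduce. The group sizes can be checked.

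**Reproducing the group sizes.** With n per arm = [1.96·√(2p̄(1−p̄)) + 0.8416·√(p₁(1−p₁)+p₀(1−p₀))]² / (p₁−p₀)²:
- 59.6% vs 37.0%: (1.385 + 0.579)² / 0.226² = 75.6, so 76; 76/0.85 = 89.4, so 90 per arm and 180 in total, as stated.
- 91.6% vs 79.0%: (0.982 + 0.415)² / 0.126² = 122.8, so 123; 123/0.85 = 144.7, so 145 per arm and 290 in total, against 288 stated. This is a rounding matter of two participants.

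**What the pooled contrast estimates.** If d₁ and d₂ are the AE risk differences (MSNP minus placebo) without and with paroxetine, the pooled difference is

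D = (90·d₁ + 144·d₂)/234 = 0.385·d₁ + 0.615·d₂.

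D is exactly zero only when d₂ = −0.625·d₁ (90/144 = 0.625).

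**Power under assumed AE rates.** The rates below are illustrations. Power is by simulation of the uncorrected chi-square test, with every participant starting treatment and contributing AE data.

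| Assumed AE rates, placebo → MSNP | D (points) | Pooled test | Non-paroxetine stratum | Paroxetine stratum |
|---|---|---|---|---|
| A: 10→25% without; 50→50% with | 13.5/234 = +5.8 | 24% | 77% | 5% (no effect) |
| B: 10→25% without; 50→40% with | (13.5−14.4)/234 = −0.4 | 4% | 77% | 40% |
| C: 10→20% without; 40→50% with | +10.0 | 64% | 47% | 40% |

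A is dilution: 40.4% vs 34.6% overall. B is masking: 34.2% vs 34.6% overall. C is the case in which pooling helps.

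A normal-approximation check for A agrees. Within the stratum, (0.15 − 1.96·0.0566)/0.0555 = 0.70, giving 76%. Pooled, (0.0577 − 1.96·0.0448)/0.0447 = −0.67, giving 25%.

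**Does adjusting for stratum help?** A Cochran–Mantel–Haenszel test still averages the two stratum effects. It rejects in about 27% of trials in A and 5% in B, so adjustment alone does not recover the stratum-specific answer.

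**Does an interaction term help?** On the risk-difference scale:
- B: SE = √((0.09+0.1875)/90 + (0.25+0.24)/144) = 0.0805, z = 0.25/0.0805 = 3.10, power Φ(3.10−1.96) ≈ 87%.
- A: SE = √((0.09+0.1875)/90 + (0.25+0.25)/144) = 0.0810, z = 0.15/0.0810 = 1.85, power about 46%.

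The interaction is a useful addition but does not replace the stratum estimates.

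**Precision within a stratum.** At 10% incidence in both arms and 90 vs 90, the 95% half-width of the risk difference is 1.96·√(2·0.1·0.9/90) = 0.088, or ±8.8 points.

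**The case against.** Three arguments deserve weight.

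First, the protocol does not say outright that AEs are tested once on pooled data. The sentence in section 2.14 covers categorical outcomes in general, four treatment conditions are defined, and randomisation is within strata, so comparisons by stratum are not excluded. This stands as a caution. Even so, the labels in section 2.9 make 234 versus 234 the natural reading, and the contrast with the primary model's interaction term supports it.

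Second, this is a condensed article, and stratum-wise AE tables and intervals are commonly left to an analysis plan. The absence of a confidence interval would not be a finding by itself. The point is that the article does fix a method, and the fixed method does not match the article's own aims.

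Third, pooling is not always a loss, as scenario C shows. This is correct and is the reason to keep the overall comparison.

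Two stronger readings are tempting, and the documents support neither. A reader might infer that the two safety aims point in opposite directions, so that harm and benefit must offset each other. The first aim is neutral, only the second names a direction and it is exploratory, and section 2.7 does not confine gastrointestinal events to one stratum. Exact offsetting needs d₂ = −0.625·d₁, and no AE rates are given. A reader might also infer that a non-significant test will be taken as proof of safety. No section states that rule. Section 2.16 bases early termination on judged risk and benefit, and section 2.7 provides grading and causality assessment of individual events.

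**Conclusion.** The point holds in a limited form. On its natural reading, the stated AE comparison tests a pooled null that corresponds to neither safety aim, whatever the true AE rates. How much this matters depends on rates that the protocol does not give. Under the assumed rates, an excess confined to MSNP alone is detected with 24% power pooled and 77% within its stratum. With an assumed reduction in the paroxetine stratum as well, the pooled test rejects in 4% of trials. With effects in the same direction the pooled test does better than either stratum (64% against 47% and 40%). The conclusion is therefore that pooling can dilute or mask a stratum-specific effect, not that it will. The primary efficacy analysis is untouched.

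**What to change.** In section 2.14, replace the AE part of the categorical-outcome sentence with text to this effect:

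*AE incidence (any AE, SAEs, gastrointestinal AEs and the listed paroxetine reactions) will be reported within each paroxetine stratum as the risk difference, MSNP minus placebo, with a 95% confidence interval (score or exact method where events are sparse). A treatment-by-paroxetine interaction will be estimated for any-AE incidence. The overall comparison of MSNP-containing and placebo-containing arms is supportive. Statements on the safety of MSNP monotherapy will rest on the non-paroxetine stratum, and statements on mitigation of side effects on the paroxetine stratum.*

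This needs wording and a few extra tables, with no new data or participants, and it can be settled before recruitment, anticipated for June 2026. The cost is precision: intervals within a stratum are wider than pooled ones, about ±8.8 points at 10% incidence with 90 versus 90. A statement on monotherapy safety will then carry the uncertainty that this stratum actually has.

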### Trial status

2.15

Participant recruitment for this clinical trial is anticipated to commence in June 2026.

### Trial termination criteria

2.16

The trial may be suspended or terminated early if any of the following circumstances occur: (1) unexpected safety risks judged to be related to the study intervention and sufficient to affect participant safety; (2) an unexpectedly high incidence of serious AEs indicating that the overall risk–benefit profile is no longer acceptable; (3) major protocol violations or serious deficiencies in trial conduct that may compromise participant safety, data integrity, or the validity of trial results; (4) failure to achieve adequate recruitment or follow-up despite corrective measures, making the study objectives unattainable; or (5) a decision by the ethics committee, regulatory authority, or data monitoring committee indicating that continuation of the trial is inappropriate. Any decision to suspend or terminate the trial will be documented and reported to relevant parties, and appropriate safety follow-up will be provided for enrolled participants.

## Discussion

3

This study is a nationwide, multicenter, randomized, double-blind, placebo-controlled clinical trial designed to systematically evaluate the efficacy, safety, and potential mechanisms of MSNP in the treatment of postoperative mild-to-moderate depression in patients with NSCLC. The trial is based on a rigorous methodological design, integrating multidimensional efficacy assessments and omics-based mechanistic analyses. It aims to address the current lack of high-quality clinical evidence for TCM interventions in depression.

Grounded in real-world clinical practice, this study adopts a design that ensures both scientific rigor and clinical applicability. First, it employs a strict randomized, double-blind, placebo-controlled design and is conducted collaboratively across nine research centers in different provinces of China, ensuring strong external validity and generalizability. Second, the study stratifies participants based on concomitant paroxetine use, with the aim of achieving two key objectives. The first is to evaluate the efficacy and safety of MSNP monotherapy as a viable alternative for patients who are unwilling or unable to tolerate antidepressants. The second is to explore the potential synergistic effects or mitigation of side effects when MSNP is combined with standard pharmacotherapy. This dual-scenario design enables a comprehensive appraisal of MSNP’s clinical value in personalized treatment strategies. In addition, the study includes multidimensional efficacy endpoints covering depression, anxiety, sleep disturbance, fear of recurrence, quality of life, and cancer survival. Multiple timepoint assessments are used to capture the psychological and physiological effects of MSNP in a comprehensive manner.

The pathogenesis of depression is a highly complex biological process involving several key mechanisms, including inflammation, HPA axis dysregulation, neurotransmitter imbalance, reduced BDNF levels, gut microbiota disturbances, and metabolic abnormalities. TCM is characterized by multi-component, multi-target, and multi-pathway pharmacological properties, which align well with the multifactorial and systemic pathology of depression. MSNP may exert its effects by simultaneously regulating multiple biological pathways involved in the disease process (Li et al., 2020). Studies have shown that SNP may prevent reserpine-induced depression in rats by reducing IL-1β, IL-6, and TNF-α levels in serum and hippocampus, thereby alleviating inflammation (Zong et al., 2020). Other studies indicate that SNP may produce antidepressant effects by increasing the expression of 5-HT1A receptors and BDNF in the hippocampus (Cao et al., 2019). Chaihu-Shu-Gan-San (CSGS) is another classical antidepressant TCM formula with a composition similar to MSNP and sharing the treatment principle of soothing the liver and regulating qi. Multiple animal studies suggest that CSGS may alleviate depressive symptoms through several biological pathways (Yu et al., 2020; Ma et al., 2022; Han et al., 2021), such as modulating gut microbiota (e.g., increasing *Parabacteroides distasonis*), regulating blood metabolites (e.g., elevating bile acid levels), regulating neurotransmitters (e.g., increasing hippocampal levels of DA, NE, and 5-HT), suppressing HPA axis hyperactivity (e.g., reducing serum CORT), and attenuating inflammatory responses (e.g., lowering serum IL-1β and IL-6). Based on this preliminary evidence, the present study will apply multi-omics approaches to comprehensively investigate the biological mechanisms of MSNP, focusing on inflammation, neurotransmitters, HPA axis function, BDNF levels, gut microbiota composition, and serum metabolic profiles.

Several potential limitations should be noted. First, the study does not include a head-to-head comparison between MSNP and standard antidepressants. If the results are promising, future trials may consider such comparative studies. Second, this trial focuses on patients with postoperative depression after NSCLC surgery. Future studies could expand to include other cancer types or general depressive populations to further examine the generalizability and clinical applicability of MSNP. Third, current mechanistic investigations are primarily based on peripheral biomarkers. Future research may incorporate neuroimaging techniques, such as functional magnetic resonance imaging and positron emission tomography, to assess MSNP’s impact on brain network activity and further elucidate its central mechanisms of action.

In summary, by integrating a rigorously designed randomized controlled trial with systematic omics-based analyses, this study aims to construct a coherent evidence chain linking clinical efficacy with biological mechanisms. The findings are expected to support the clinical application of MSNP in the treatment of postoperative mild-to-moderate depression in NSCLC patients and contribute to the modernization and translational development of TCM interventions for cancer-related psychological disorders.
